# Effect of pneumoperitoneum pressure and the depth of neuromuscular block on renal function in patients with diabetes undergoing laparoscopic pelvic surgery: study protocol for a double-blinded 2 × 2 factorial randomized controlled trial

**DOI:** 10.1186/s13063-020-04477-x

**Published:** 2020-06-29

**Keywords:** Diabetes, Pneumoperitoneum pressure, Neuromuscular block, Renal injury, Renal protection, Laparoscopic surgery

## Abstract

**Background:**

Patients with diabetes mellitus are at a high risk of developing postoperative acute kidney injury. For patients receiving laparoscopic surgery, standard-pressure pneumoperitoneum (SPP) currently applied in clinical practice also undermines renal perfusion. Several studies have shown that low-pressure pneumoperitoneum (LPP) might reduce pressure-related ischemic renal injury. However, LPP may compromise the view of the surgical field. Previous studies have indicated that deep neuromuscular blockade (NMB) can ameliorate this issue. However, the conclusion is still uncertain. The hypothesis of this study is that the joint use of LPP and deep NMB can reduce perioperative renal injury in diabetic patients undergoing laparoscopic pelvic surgery without impeding the view of the surgical field.

**Methods:**

This is a double-blinded, randomized controlled trial using a 2 × 2 factorial trial design. A total of 648 diabetes patients scheduled for major laparoscopic pelvic surgeries at Peking Union Medical College Hospital will be randomized into the following four groups: SPP (12–15 mmHg) + deep-NMB (post-tetanic count of 1–2) group, LPP (7–10 mmHg) + deep-NMB group, SPP + moderate-NMB (train-of-four of 1–2) group, and LPP + moderate-NMB group. The primary outcome is serum cystatin C level measured before insufflation, after deflation, 24 h postoperatively, and 72 h postoperatively. The secondary outcomes are serum creatinine level, intraoperative urine output, erythrocytes in urinary sediment, renal tissue oxygen saturation, Leiden’s surgical condition rating scale, surgery duration, and occurrence of bucking or body movement.

**Discussion:**

This study will provide evidence for the effect of LPP on renal function protection in patients with diabetes undergoing laparoscopic pelvic surgery. The trial can also help us to understand whether deep NMB can improve surgical conditions.

**Trial registration:**

ClinicalTrials.gov: NCT04259112. Prospectively registered on 5 February 2020.

## Background

Globally, the number of diabetes mellitus patients has quadrupled in the last 30 years, and China has the fastest growing epidemic of type 2 diabetes [1]. More than half of these patients suffer from at least one diabetic complication [2]. In China, the prevalence of diabetic kidney disease is as high as 24.3% in patients with type 2 diabetes [3], making it the leading cause of end-stage renal disease (ESRD) [4]. Renal failure accounts for approximately 10% of mortality in the presence of type 2 diabetes [5]; thus, the progression of diabetic nephropathy should be prevented as early as possible.

Postoperative acute kidney injury (AKI) affects 13–20% of patients undergoing major surgery [6, 7] and is associated with substantial morbidity and mortality [8, 9]. Pre-existing chronic kidney disease, including diabetic kidney disease, is associated with an increased risk of postoperative AKI [10]. Furthermore, diabetes is also an independent risk factor for postoperative AKI [11, 12]; thus, patients with diabetes deserve particular attention in terms of perioperative renal protection. According to the 2012 Kidney Disease: Improving Global Outcomes (KDIGO) criteria, AKI refers to the sudden decrease in renal function, defined by an elevation in serum creatinine (Cr) level or a decrease in urine output [13]. However, since an increase in Cr level may occur 2–3 days after renal ischemia [14], more sensitive biomarkers are necessary for the early recognition and prevention of AKI. Serum cystatin C (CysC) is one of these biomarkers [15]. In addition, renal oxygen saturation is also a promising predictor for AKI [16, 17].

Patients undergoing abdominal surgery are more likely to develop AKI than those undergoing other noncardiac, nonvascular surgeries [12, 18]. Pneumoperitoneum is necessary for better visualization and manipulation in laparoscopic surgery. The increased intra-abdominal pressure (IAP) induced by pneumoperitoneum can activate the renin-angiotensin-aldosterone system (RAAS) and cause renal vascular and parenchymal compression [19], which will further undermine renal perfusion and create ischemic insults [20]. Prior literature has demonstrated the association between increased IAP and AKI in critically ill patients after abdominal surgery [21, 22]. Intraoperative oliguria and diminished glomerular filtration rates have also been observed [23]. These changes deteriorate with increases in pressure and extended durations [23]. However, several studies have reported conflicting results, indicating that laparoscopic surgery does not carry an additional risk of postoperative AKI [24–26]. Therefore, high-quality evidence is needed for a better understanding.

Low-pressure pneumoperitoneum (LPP, 7–10 mmHg) is recommended to minimize the ischemic organ injury caused by standard-pressure pneumoperitoneum (SPP, 12–15 mmHg) [27]. LPP has been successfully used in a series of abdominal and pelvic surgeries, such as laparoscopic hysterectomy, cholecystectomy, and adrenalectomy [28–31]. However, LPP compromises the working space and surgical field, leading to prolonged surgical durations [32]. Fortunately, studies have shown that deep neuromuscular blockade (NMB) can ameliorate this issue [33, 34] and facilitate the use of LPP [35–37]. However, such effects are still controversial [38, 39]; thus, further studies are still required.

Therefore, the objective of this study is to assess the effect of LPP *versus* SPP on renal function protection in patients with diabetes undergoing laparoscopic pelvic surgery and to evaluate whether deep NMB can improve surgical conditions compared with moderate NMB. We hypothesize that the use of LPP, facilitated by deep NMB, can improve postoperative renal function after laparoscopic pelvic surgeries.

## Methods/design

### Study design

This is a double-blinded, randomized controlled trial using a 2 × 2 factorial trial design, aiming to investigate the effect of pneumoperitoneum pressure and the depth of NMB on renal function in patients with diabetes undergoing laparoscopic pelvic surgery. Participants will be divided into the following four groups: (1) standard PP + deep NMB (S + D), (2) low PP + deep NMB (L + D), (3) standard PP + moderate NMB (S + M), and (4) low PP + moderate NMB (L + M) (Table 1). Deep NMB and moderate NMB are defined as a post-tetanic count (PTC) of 1–2 and a train-of-four (TOF) of 1–2, respectively. The pneumoperitoneum pressure will be set to 7–10 mmHg in the LPP groups and 12–15 mmHg in the SPP groups. We assume that no interaction is present between the two interventions being assessed on the primary outcome. The protocol is in accordance with the Standard Protocol Items: Recommendations for Interventional Trials (SPIRIT) guidelines (Additional file 1). The study flow chart is demonstrated in Fig. 1, and the overall schedule of enrollment, interventions, and assessments is shown in Table 1. All the members of the research team will be trained on the procedures prior to study commencement.

**Table 1 Tab1:**
[figure not shown]
Schedule of enrollment, interventions, and assessments

^*^Baseline variables, ^#^outcome variables, ^**+**^intraoperative factors

**Fig. 1 Fig1:**
[figure not shown]
Flow chart of study design

### Settings

The study will be conducted in Peking Union Medical College Hospital (PUMCH), which is a tertiary general teaching hospital with 2200 beds in Beijing, China. An average of 20 elective pelvic surgeries are performed by five surgeons on each working day. The Ethics Committees of this hospital (reference number: ZS-1654) approved the trial.

### Participant selection

All patients scheduled for elective laparoscopic pelvic surgeries under general anesthesia will be screened for eligibility by an investigator who will not be involved in the process of randomization, intervention, data collection, or outcome assessment. Patients will be considered eligible if they meet the inclusion criteria and do not meet the exclusion criteria. Written informed consent will be obtained after evaluation.

The inclusion criteria are as follows:
Age 18–70 yearsAmerican Society of Anesthesiologist (ASA) Classification II-IIIDiagnosis of diabetes mellitusEstimated surgery duration > 3 h. The estimated surgery duration will be determined by the average duration of the same type of surgery by the same surgeon in the last year.

The exclusion criteria are as follows:
Not willing to participate in the study or unable to sign informed consentDiagnosis of any kidney diseases other than diabetic kidney diseasesSevere renal insufficiency defined as serum Cr > 2 times the upper limit of normal, urine output < 0.5 ml/kg/h, or estimated glomerular filtration rate (eGFR) < 60 ml/hSevere liver, lung or heart dysfunctionKnown or suspected neuromuscular diseaseUse of drugs that may affect neuromuscular block monitoringSevere diabetic neuropathy or any other peripheral neuropathyKnown or suspected allergy to general anestheticsFamily history of malignant hyperthermiaPrevious history of pelvic surgery

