### Interventions

#### Anesthesia

An intravenous (IV) cannula will be inserted for the administration of anesthetic drugs. All enrolled patients will receive total intravenous anesthesia (TIVA). Intraoperative monitoring will include electrocardiography (ECG), pulse oximetry (SpO_2_), invasive arterial blood pressure (ABP), stroke volume (SV) and stroke volume variation (SVV) measured by LiDCO-rapid™, inspiratory and expiratory gas analysis, pressure of end tidal carbon dioxide (PetCO_2_), tidal volume, airway pressure, bispectral index (BIS), cerebral oxygen saturation, renal tissue oxygen saturation, nasopharyngeal temperature, and peripheral skin temperature. Anesthesia will be induced via the target-controlled infusion (TCI) of propofol (at an effect-site concentration of 6 μg/ml) and a bolus injection of 2–3 μg/kg fentanyl or 0.2–0.3 μg/kg sufentanil. Endotracheal intubation will be performed after the administration of a predefined dose of rocuronium based on the grouping. Anesthesia will be maintained with a TCI of propofol and continuous infusion of remifentanil. Mean blood pressure and heart rate fluctuations will be maintained within 20% of baseline, and the targeted BIS value will be 50–60. Fluid infusion will be adjusted to maintain SV < 10% and SVV < 13. Patients will be mechanically ventilated using a volume-controlled pattern with a tidal volume of 7–9 ml/kg and a frequency of 10–13/min. PetCO_2_ will be maintained between 35 and 45 mmHg. Forced-air warming will be used to maintain central and peripheral skin temperatures ≥ 36 °C and 32 °C, respectively.

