### Sample size calculation and statistical analysis

A previous study [15] reported that the standard deviation of serum CysC level after laparoscopic procedures is 0.738 ± 0.186 mg/dl. For a CysC difference of 0.05 mg/dl to be considered clinically significant, a power analysis program (G* power 3.1) calculated that a total sample size of 582 patients is needed to achieve 90% power at the 5% significance level. Considering a 10% dropout rate, a total of 648 patients (162 per group) is necessary. Approximately 5000 patients are scheduled for elective major pelvic surgery in PUMCH every year, and approximately 15% of them have diabetes; thus, one year is estimated as necessary to achieve adequate participant enrollment.

We will first compare the two SPP groups with the two LPP groups and then compare the two deep-NMB groups with the two moderate-NMB groups. Finally, all four groups will be compared.

The baseline characteristics and intraoperative factors of the enrolled patients will be evaluated using descriptive analysis. Continuous variables will be summarized as the mean  ±  standard deviation (SD) or median (interquartile range, IQR) as appropriate, whereas categorial variables will be summarized as the number (percentage). The baseline characteristics will be compared between groups using the standardized difference, and a standardized difference < 0.2 will be considered an acceptable balance between groups. Unbalanced variables at baseline will be included in the ANOVA or mixed-effects model to adjust for the potential confounding effect.

Considering the multiple measures of CysC, Cr, surgical condition rating scale, and renal tissue oxygen saturation at different time points, the effect of intervention in the whole timeframe will be analyzed by a mixed-effects model. Other continuous variables will be compared by two-sided independent Student’s t tests or the Mann–Whitney U test, as appropriate. Categorical variables will be analyzed by a Chi-square test or Fisher’s exact test, as appropriate. The Bonferroni method will be used to correct the potential increase in the probability of a type I error when analyzing the differences between the four groups.

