### Adverse events

We anticipate that the potential risk of this study is minimal. First, to minimize the risks of failure in performing surgeries under LPP, we will exclude patients with a history of pelvic procedures, which may lead to adhesions and may increase the manipulation difficulty. Furthermore, all five surgeons involved have at least 10 years of experience in performing laparoscopic surgeries. Second, SPP has been safely used in PUMCH for more than 20 years. Patients with severe liver, heart, lung and kidney dysfunction will be excluded; thus, the potential risk of irreversible ischemic organ injury caused by SPP should be extremely low. Third, rocuronium is mainly metabolized in the liver, and no evidence exists to show that the dosage used in deep NMB has renal toxicity in patients without ESRD. Finally, to avoid residual paralysis, 6 mg neostigmine will be given at the end of surgery to antagonize the residual muscle relaxant, and patients will not be extubated until the TOF ratio is > 90%.

Adverse events information will be collected spontaneously from the participants during the follow-up and recorded in CRFs with details (time, severity, treatment, outcome, and the relationship to the intervention). Serious adverse events will be reported to the medical ethics committee.

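### The eGFR limb of the renal exclusion is printed in ml/h (60 ml/h is 1 ml/min), so that limb does nothing; the stroke-volume fluid target also lacks a usable unit

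*Protocol article*

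**What the plan says.** **Renal exclusion.** Participant selection excludes severe renal insufficiency and defines it by any one of three findings: serum creatinine above twice the upper limit of normal, urine output below 0.5 ml/kg/h, "or estimated glomerular filtration rate (eGFR" below 60 ml/h. A separate criterion excludes kidney disease by diagnosis but exempts diabetic kidney disease. No other section gives an eGFR limit or unit.

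**Safety argument.** The Adverse events section relies on the exclusions: "Patients with severe liver, heart, lung and kidney dysfunction will be excluded". From this it concludes that the risk of irreversible organ injury under standard pressure is extremely low.

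**Fluid rule.** The Anesthesia section lists among the monitored quantities "stroke volume (SV) and stroke volume variation (SVV) measured by LiDCO-rapid™". It then sets the target: "Fluid infusion will be adjusted to maintain SV < 10% and SVV < 13".

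**The concern.** An eligibility limit is something screening staff apply. If its unit makes it impossible to meet, either they apply it literally and it excludes nobody, or each screener substitutes the unit that he or she thinks was meant. The two readings admit different patients. Here the difference falls on kidney function, in a trial whose primary outcome is serum cystatin C and whose population is chosen for its renal risk. Because diabetic kidney disease is allowed in, the numerical renal limits are what decide entry for those patients.

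The fluid rule is a similar but lesser matter. It is applied during every operation, and the Discussion itself names infused fluid and hemodynamic indices as factors that may affect renal perfusion. A target that cannot be read as printed leaves staff to choose their own.

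**Working it through.** **1. The unit conversion**
- Input: eGFR limit of 60 ml/h (Participant selection).
- 60 ml/h ÷ 60 min/h = 1 ml/min.
- If ml/min was meant: 60 ml/min × 60 min/h = 3600 ml/h.
- Ratio of the two limits: 3600 ÷ 60 = 60.

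The urine-output limb immediately before it is correctly stated per hour. A carry-over of that unit is a plausible explanation, but the article does not confirm it.

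**2. What each reading does to eligibility**

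The three limbs are joined by 'or', so one is enough to exclude. In each row below, urine output is at or above 0.5 ml/kg/h and all other criteria are met.

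| Patient | Limit read as 60 ml/h (1 ml/min) | Limit read as 60 ml/min |
|---|---|---|
| Creatinine above 2 × upper limit | excluded by creatinine | excluded by creatinine |
| Creatinine not above 2 × upper limit, eGFR at least 1 but below 60 ml/min | **eligible** | **excluded** |
| Creatinine not above 2 × upper limit, eGFR 60 ml/min or more | eligible | eligible |

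The readings differ only in the middle row. The article gives no distribution of eGFR in the screened population, so the size of that group cannot be calculated. The Background puts diabetic kidney disease at 24.3% of Chinese patients with type 2 diabetes. That shows such patients will be met at screening, but it does not estimate the middle row.

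**3. The fluid target**

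The article defines SV as stroke volume, which is a volume. The target for it is a percentage, and no reference quantity (baseline, previous value, response to a fluid bolus) is given. That half of the rule cannot be evaluated from a measurement as printed. SVV is a variation index printed without a unit. Its meaning is not in real doubt, so that omission is cosmetic.

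**4. Does either slip reach the sample size?**
- Inputs (Sample size calculation and statistical analysis): SD from "serum CysC level after laparoscopic procedures is 0.738 ± 0.186 mg/dl", difference 0.05 mg/dl, 90% power, two-sided 5%.
- n per pressure level = 2 × (1.960 + 1.282)² × 0.186² ÷ 0.05² = 290.8, rounded up to 291. The total is 2 × 291 = 582, as stated. The t-test version gives 584.
- Dropout: 582 ÷ 0.90 = 646.7. The next multiple of four is 648, or 162 per group, as stated.

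eGFR is not an input to any of these steps. Correcting its unit leaves 582 and 648 unchanged.

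**The case against.** The best reply is that this is an evident misprint in a condensed article: a limit of 1 ml/min is so plainly useless that nobody would take it as intended, and two other renal limbs still work. Much of this stands. The slip is probably typographical, and the renal exclusion as a whole is not void. What the reply does not settle is which limit staff should apply instead. The article never states it, and the choice changes who is eligible.

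Three stronger readings are tempting, and the document supports none of them.

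- **Patients with severe kidney dysfunction would be enrolled.** The creatinine and urine-output limbs still exclude severe dysfunction, so the statement in Adverse events is not falsified. What a literal reading loses is the exclusion of reduced eGFR with creatinine not above twice the limit.
- **Admitting these patients would widen the spread of cystatin C and erode power.** That needs a larger SD than 0.186, and the article offers no source for one. It does not link the SD to an eGFR limit, nor say that the study supplying the 0.186 used one. Any power figure built this way would rest on an invented input.
- **The loose fluid rule would bias the comparison.** The rule is the same in all four groups. SV, SVV and the volumes infused are recorded, and the Discussion foresees checking balance and adjusting if necessary. Looser fluid management would be expected to add noise; no between-group bias is evident.

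On stroke volume, the preceding sentence in the Anesthesia section limits blood pressure and heart rate relative to baseline, so a change in SV of less than 10% is a reasonable guess at the meaning. It remains a guess.

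**Conclusion.** The point holds in a limited form. The eGFR limb of the renal exclusion is printed with a limit of 1 ml/min and is inoperative. If ml/min was intended, the printed limit is too low by a factor of 60. The consequence is confined to patients with reduced eGFR whose creatinine and urine output do not exclude them: eligible as written, excluded under a 60 ml/min limit. Their number is unknown from the article. That ml/min (or ml/min/1.73 m²) was meant is an assumption for the clinical team to confirm.

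The stroke-volume target is a secondary error of the same kind: half of the fluid rule cannot be followed as printed. The sample size and analysis are unaffected. This should be corrected because it is a working eligibility limit in a trial of renal function, but it does not threaten the design.

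**What to change.** Before recruitment starts (1 August 2020 according to Trial status):

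- In Participant selection, replace ml/h in the eGFR limb with the unit in which the laboratory reports eGFR, presumably ml/min or ml/min/1.73 m². The clinical team should confirm both the unit and that 60 is the value they want in it, alongside the creatinine and urine-output limbs.
- In Anesthesia, restate the SV target as something measurable, for example a change in SV relative to a named reference if that is what was meant, and give SVV its unit.
- Check that the case report form, screening log and registry entry carry the same corrected wording.

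The cost is a few words in two sentences. Nothing in the sample size, randomization or analysis has to change.

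If any patient has already been screened against the printed limit, note which reading was used, so that the enrolled population can be described correctly.

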### Randomization and blinding

After enrollment, just prior to the surgery, the patients will be randomized by a statistician without the knowledge of random allocation in a balanced manner to one of the four groups. The allocation sequence will be computer-generated using random block sizes and will be kept in an opaque sealed envelope. These assignment envelopes will only be opened by a nurse, who will set the pneumoperitoneum pressure, prepare the muscle relaxant, and monitor the depth of NMB. Therefore, participants, anesthesiologists, surgeons, and outcome assessors will all be blinded to the allocation throughout the trial.

### Interventions

#### Anesthesia

An intravenous (IV) cannula will be inserted for the administration of anesthetic drugs. All enrolled patients will receive total intravenous anesthesia (TIVA). Intraoperative monitoring will include electrocardiography (ECG), pulse oximetry (SpO_2_), invasive arterial blood pressure (ABP), stroke volume (SV) and stroke volume variation (SVV) measured by LiDCO-rapid™, inspiratory and expiratory gas analysis, pressure of end tidal carbon dioxide (PetCO_2_), tidal volume, airway pressure, bispectral index (BIS), cerebral oxygen saturation, renal tissue oxygen saturation, nasopharyngeal temperature, and peripheral skin temperature. Anesthesia will be induced via the target-controlled infusion (TCI) of propofol (at an effect-site concentration of 6 μg/ml) and a bolus injection of 2–3 μg/kg fentanyl or 0.2–0.3 μg/kg sufentanil. Endotracheal intubation will be performed after the administration of a predefined dose of rocuronium based on the grouping. Anesthesia will be maintained with a TCI of propofol and continuous infusion of remifentanil. Mean blood pressure and heart rate fluctuations will be maintained within 20% of baseline, and the targeted BIS value will be 50–60. Fluid infusion will be adjusted to maintain SV < 10% and SVV < 13. Patients will be mechanically ventilated using a volume-controlled pattern with a tidal volume of 7–9 ml/kg and a frequency of 10–13/min. PetCO_2_ will be maintained between 35 and 45 mmHg. Forced-air warming will be used to maintain central and peripheral skin temperatures ≥ 36 °C and 32 °C, respectively.

